### Statistical Analysis

The primary efficacy analysis will be based on the time from randomization assignment to the first occurrence of any component of MACE. Data will be analyzed using intention-to-treat analysis (ITT) and per protocol (PP) to assess the efficacy and safety of evolocumab in combination with moderate-intensity statin therapy. The superiority of evolocumab will be assessed for all efficacy endpoint. Continuous variables with an approximately normal distribution will be reported with mean±standard deviation (mean±SD), and differences between the two treatment arms will be tested using independent sample t-test. For continuous variables that are not normally distributed, the median and interquartile range (IQR) will be given, and the nonparametric Mann–Whiney U test will be conducted to test for differences between treatment arms. Discrete variables will be reported with counts and percentage for each arm, and differences between arms will be examined using Fisher’s exact test. In order to compare MACE differences, Kaplan–Meier survival curve analysis will be performed, and hazard ratio (HR) and 95% CI will be calculated. Log-rank tests will also be performed to evaluate the differences in significance and verify treatment efficacy.

The ITT population will include all randomized patients and the PP population will include all randomized patients who complete the entire study. Subjects with missing data will be excluded from the corresponding analysis. Logistic regression will be used to analyze differences in the central effect sizes.

Results of the proposed study will be analyzed using SAS 9.2 or higher version (SAS Institute, North Carolina, United States) software. All statistical tests will be two-tailed unless otherwise indicated or presented with a 95% confidence interval (CI), and statistical significance will be established as *p*<0.05.

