## Abstract

**Background:** Several studies have demonstrated that using a higher dose of statin can easily induce liver injury and myopathy. Low-density lipoprotein cholesterol (LDL-C) is a well-established modifiable risk factor for cardiovascular disease; however, the large majority of Chinese patients cannot meet the target level of LDL-C recommended by the Chinese expert consensus. Evolocumab has been demonstrated to reduce LDL-C by approximately 60% in many studies. Nevertheless, whether combined evolocumab and moderate-intensity statin is as effective in lowering LDL-C and decreasing incidence of MACE in Chinese patients presenting with the acute phase of acute coronary syndrome (ACS) remains unknown. Therefore, the “Evolocumab added to Moderate-Intensity Statin therapy on LDL-C lowering and cardiovascular adverse events in patients with Acute Coronary Syndrome” (EMSIACS) is conducted.

**Methods:** The EMSIACS is a prospective, randomized, open-label, parallel-group, multicenter study involving analyzing the feasibility and efficacy of evolocumab added to moderate-intensity statin therapy on lowering LDL-C levels in adult Chinese patients hospitalized for acute phase ACS. The sample size calculation is based on the primary outcome, and 500 patients will be planned to recruit. Patients are randomized in evolocumab arm (evolocumab 140mg every 2weeks plus rosuvastatin 10mg/day or atorvastatin 20mg/day) and statin-only arm (rosuvastatin 10mg/day or atorvastatin 20mg/day). The primary outcome is the percentage change in LDL-C in weeks 4 and week 12 after treatment. The secondary outcome is the occurrence of MACE after 12weeks and 1year of treatment.

**Discussion:** If the EMSIACS trial endpoints prove statistically significant, the evolocumab added to moderate-intensity statin therapy will have the potential to effectively lower subjects’ LDL-C levels, especially for the Chinese patients with acute phase ACS. However, if the risk of MACE is not significantly different between the two groups, we may extend follow-up time for secondary outcome when the clinical trial is over.

**Clinical trial registration**: The study is registered to ClinicalTrials.gov (NCT04100434), which retrospectively registered on November 24, 2020.

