### Aims of the Study

The overall purpose of EMSIACS study is to determine the feasibility, safety, and efficacy of the evolocumab added to moderate-intensity statin therapy, using the statin-only therapy as the control arm, on LDL-C level variability between baseline and 1-year follow-up in patients with acute phase ACS. This study was designed to address two principal research questions:

We determine the effects of the evolocumab added to moderate-intensity statin therapy on MACE.We plan to identify the appropriate ACS patient population for the administration of evolocumab in combination with standard statin therapy.

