### Main Outcome Measures

Subjects of the present study will receive 24 treatments after being enrolled, and data of laboratory examinations will be evaluated at 72h and weeks 1, 4, 8, 12, 24, and 48 after intervention (Table 1; Figure 1).

The primary outcome of the present study will be the mean percentage change of the LDL-C level between baseline and weeks 4 and 12 post-treatment (Table 1; Figure 1). The secondary outcome will be MACE (defined as coronary heart disease death, nonfatal myocardial infarction, hospitalization for unstable angina, unplanned coronary revascularization, and stroke) assessed at week 12 and week 48 post-treatment (Table 1; Figure 1). The following issues will also be investigated: (1) the proportion of patients with LDL-C<70mg/dl, <55mg/dl and<40mg/dl during the study period; (2) patients’ quality of life as evaluated with the PROMIS 10 scale at week 12 and week 48 post-treatment; and (3) the percentage change in inflammatory biomarkers including but not limited to high-sensitivity C-reactive protein (hsCRP), interleukin (IL)-1β and IL-6, from baseline to weeks 48 (Table 1; Figure 1). Other biomarkers that exhibit significant difference between the two study arms will be investigated retrospectively after the trial.

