### Sample Size Calculation

This is a superiority trial, and the sample size calculation is based on the primary efficacy endpoint, namely the percentage of change in LDL-C levels from baseline to week 4 after randomization. In order to have 90% power to detect clinically meaningful differences in treatment effects with a one-sided significance level of 5% (α=0.05), a sample size of 193 patients is required for each treatment arm. Assuming that the drop-out rate is 20%, this study aims to enroll approximately 484 patients, with 242 patients in the evolocumab plus statin arm and 242 in the statin-only arm. Therefore, the proposed study is expected to enroll a total of 500 patients with acute phase ACS, with 250 patients in each treatment arm.

The number of patients enrolled from each hospital is based on the bed size of each hospital. The Tianjin Chest Hospital plans to enroll 220 patients, and the remaining seven hospitals each will enroll 40 patients.

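### The Statistical Analysis section makes time to first MACE the primary efficacy analysis, but the primary outcome and the 90% power calculation concern percentage change in LDL-C

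*Protocol article*

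**What the plan says.** Four sections of the protocol article bear on which comparison is primary.

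- Abstract, Methods: "The primary outcome is the percentage change in LDL-C in weeks 4 and week 12 after treatment"; "The sample size calculation is based on the primary outcome, and 500 patients will be planned to recruit"; "The secondary outcome is the occurrence of MACE after 12weeks and 1year of treatment".
- Main Outcome Measures: "The primary outcome of the present study will be the mean percentage change of the LDL-C level between baseline and weeks 4 and 12" post-treatment. The same paragraph continues: "The secondary outcome will be MACE", assessed at weeks 12 and 48.
- Sample Size Calculation: the trial is sized on "the primary efficacy endpoint, namely the percentage of change in LDL-C levels from baseline to week 4 after randomization", with 90% power at a one-sided 5% level. This gives 193 per arm, 484 in total after 20% drop-out, and a planned 500.
- Statistical Analysis: "The primary efficacy analysis will be based on the time from randomization assignment to the first occurrence of any component of MACE". The section goes on to specify Kaplan–Meier curves, a hazard ratio with 95% CI and log-rank tests for MACE. It never mentions LDL-C, which is covered only by the general wording on t-tests and Mann–Whitney tests for continuous variables.

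Aims of the Study adds some weight to the MACE side. The first of its two principal research questions is: "We determine the effects of the evolocumab added to moderate-intensity statin therapy on MACE".

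**The concern.** A confirmatory trial is judged on its primary analysis, and its power statement is meaningful only for that analysis. Here the outcome and sample-size sections point to a continuous lipid measure, while the analysis section points to a time-to-event composite that the outcome section calls secondary.

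Two things are at stake. First, anyone following the Statistical Analysis section as written would judge the trial on an endpoint for which no power has been calculated. Second, the trial is open-label and the text supports either endpoint as primary, so the choice could be made after results are known. The Abstract's Discussion makes this more than theoretical. It says follow-up for MACE may be extended if the arms do not differ significantly on it. For a secondary outcome that is an exploratory extension; if MACE is primary, it is a results-driven extension of the primary analysis.

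**Working it through.** **1. The plan's own figures.** The drop-out step reproduces: 193 / (1 − 0.20) = 241.25, rounded up to 242 per arm, or 484 in total. The site allocation also agrees: 220 + 7 × 40 = 500.

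The 193 itself cannot be recomputed, because no LDL-C difference or SD is stated. It can be solved backwards with d = √(2/n) × (z for α + z for power):

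- one-sided 5%: d = √(2/193) × (1.645 + 1.282) = 0.298 SD;
- two-sided 5%: d = √(2/193) × (1.960 + 1.282) = 0.330 SD.

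Either way, taken as the continuous week-4 comparison the section names, 193 per arm corresponds to a standardised difference in means. No event rate enters it, so the 90% says nothing about a log-rank test on MACE. This step needs no assumption.

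**2. What 500 patients would give for MACE.** The documents supply no MACE rate, hazard ratio or event target, so these inputs are assumed: 48-week control risk p of 5% to 20%, hazard ratio (HR) of 0.5 to 0.85, 250 per arm (as planned), no loss to follow-up, two-sided 5%.

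- Treated-arm risk = 1 − (1 − p)^HR
- Expected events D = 250 × [p + 1 − (1 − p)^HR]
- Power (Schoenfeld) = Φ(½√D × |ln HR| − 1.96)

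Example with p = 10% and HR 0.80: D = 45.2, so power = Φ(½ × √45.2 × 0.223 − 1.96) = Φ(−1.21) = 11.3%.

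| Control risk | HR 0.85 | HR 0.80 | HR 0.70 | HR 0.60 | HR 0.50 |
|---|---|---|---|---|---|
| 5% | 5.8% | 7.6% | 12.8% | 20.7% | 32.4% |
| 10% | 8.0% | 11.3% | 21.4% | 36.8% | 56.8% |
| 15% | 10.0% | 14.9% | 29.8% | 51.2% | 74.4% |
| 20% | 12.0% | 18.5% | 38.0% | 63.4% | 85.8% |
| Events needed for 90% | 1,592 | 845 | 331 | 162 | 88 |
| Events expected at 20% risk | 93.2 | 90.9 | 86.2 | 81.3 | 76.4 |

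Even at the highest assumed risk, expected events fall short of the number needed in every column.

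**3. Sensitivity.** At the one-sided 5% level used for sizing, the range is 10.5% to 91.7%, and only the corner with 20% risk and HR 0.50 passes 90%. If only the 386 evaluable patients (2 × 193) contributed, the two-sided range would be 5.3% to 75.9%.

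**The case against.** The best defence is that the sentence is a drafting slip. The Abstract, Main Outcome Measures and Sample Size Calculation agree that LDL-C is primary, and the Abstract's Discussion expressly allows for a non-significant MACE result while calling MACE secondary. That is a fair reading of intent, and it shapes the fix. It does not remove the error: an article may omit detail from a full protocol, but condensing does not turn a secondary outcome into the primary efficacy analysis. An analysis plan that is not shown cannot correct what this text asserts.

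Several stronger readings are tempting, and the documents do not support them.

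- *The trial has almost no power for MACE.* This holds only for modest assumed effects. With no rate or hazard ratio stated, what is established is that the 90% was not calculated for MACE.
- *The trial will probably be reported as negative.* This is a prediction that depends on an unstated event rate and effect, and on which primary is followed.
- *The two LDL-C time points inflate the false-positive rate to 7.8–9.5%.* That applies only if success at either time suffices (correlation 0.8 to 0.3). The article states no such rule, and the rule for combining times is commonly left to the analysis plan.
- *Requiring both times cuts power to 74–79%.* With 200 per arm, that figure takes the effect implied by one-sided sizing and tests it two-sided. With consistent sidedness it is about 84–87%. The one-sided versus two-tailed mismatch is a separate matter.
- *Week 4 versus weeks 4 and 12 is another contradictory primary.* The sizing uses one of the two named time points. That needs clarifying but is not a conflict of the same kind.

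**Conclusion.** The contradiction stands and must be corrected before analysis. The Statistical Analysis section names a primary efficacy analysis that differs from the stated primary outcome and from the endpoint used for sizing, so the trial has no stated power for the analysis it calls primary. That conclusion rests on the text alone.

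The size of the gap rests on the assumed grid. Two-sided MACE power runs from about 6% to 86%, with 11.3% to 18.5% for HR 0.80 at control risks of 10% to 20%, and never reaches 90%. The width of the range is itself informative, since the document offers nothing with which to narrow it.

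**What to change.** Replace the opening sentence of Statistical Analysis with wording such as:

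> The primary efficacy analysis is the between-arm difference in percentage change in LDL-C from baseline, in the ITT population. Time from randomisation to first MACE is a secondary analysis. The 90% power calculation does not apply to MACE.

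Then align Main Outcome Measures, the Abstract and Sample Size Calculation. State whether week 4 alone is primary, as sized, or weeks 4 and 12 are both primary, and in the latter case how they combine. Testing week 4 first and week 12 only if week 4 succeeds is one option that keeps the existing sizing. Co-primary time points or a repeated-measures average would also be legitimate if their power is stated. Aims of the Study should be worded so that the MACE question does not read as the primary one.

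This costs wording only, with no extra patients or data.

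If the sponsor does intend MACE as primary, the Abstract, Main Outcome Measures and Sample Size Calculation must change instead. The 90% claim would be withdrawn for that endpoint, and an event-based calculation with a stated rate and hazard ratio supplied. As an illustration under assumed inputs, HR 0.70 at 10% control risk needs 331 events; the mean risk is (0.100 + 0.0711)/2 = 0.0855, so about 331/0.0855 ≈ 3,870 patients.

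### The Statistical Analysis section makes time to first MACE the primary efficacy analysis, although LDL-C change is the declared primary outcome and the only endpoint the trial was sized for

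*Protocol article*

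**What the plan says.** Five parts of the protocol article bear on which analysis decides the trial.

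- **Abstract.** "The primary outcome is the percentage change in LDL-C in weeks 4 and week 12 after treatment". MACE follows as secondary: "The secondary outcome is the occurrence of MACE after 12weeks and 1year of treatment". Its discussion paragraph uses the same ranking when it plans for an inconclusive MACE result: "if the risk of MACE is not significantly different between the two groups, we may extend follow-up time for secondary outcome".
- **Main Outcome Measures.** "The primary outcome of the present study will be the mean percentage change of the LDL-C level between baseline and weeks 4 and 12", and then "The secondary outcome will be MACE".
- **Sample Size Calculation.** "the sample size calculation is based on the primary efficacy endpoint, namely the percentage of change in LDL-C levels from baseline to week 4". The 193 per arm, the 90% power and the one-sided 5% level all belong to that endpoint. MACE is not mentioned there.
- **Statistical Analysis.** "The primary efficacy analysis will be based on the time from randomization assignment to the first occurrence of any component of MACE". MACE then gets a named method (Kaplan–Meier curves, hazard ratio with 95% CI, log-rank test). LDL-C gets no named primary analysis and falls under the general rule for continuous variables (t-test or Mann–Whitney test).
- **Aims of the Study.** The overall purpose refers to LDL-C, but the first of the two listed research questions is on MACE: "We determine the effects of the evolocumab added to moderate-intensity statin therapy on MACE". The second is about identifying the right patient population.

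**The concern.** The outcome definition and the analysis section name different primaries. The text does not declare co-primary endpoints, set a testing order or divide alpha between them. Both statements are current, and this is a conflict within the protocol, not a detail left to an analysis plan.

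At stake is what the trial's main conclusion rests on. If the analysis section is followed, the main result is a survival comparison for which no event rate, target hazard ratio or event count was set. The stated 90% power would then be read alongside an analysis it does not describe. If the outcome section is followed, the analysis section does not say which LDL-C comparison is the primary one.

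**Working it through.** **Step 1: the statements side by side**

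| Section | Primary | MACE |
|---|---|---|
| Abstract | LDL-C % change, weeks 4 and 12 | secondary |
| Main Outcome Measures | LDL-C % change, weeks 4 and 12 | secondary |
| Sample Size Calculation | LDL-C % change, week 4 | not mentioned |
| Statistical Analysis | time to first MACE | primary |

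Three sections agree on LDL-C as primary, and two of them call MACE secondary. One section contradicts them. The three also differ among themselves on the time point, which matters for the fix.

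**Step 2: the plan's own figure**

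The drop-out step reproduces: 193 / (1 − 0.20) = 241.25, so 242 per arm and 484 in total, rounded up in the plan to 500. The 193 itself cannot be reproduced, because no difference or SD is given. Solving backwards, 193 per arm with 90% power at one-sided 5% implies a standardised difference of (1.645 + 1.282) × √(2/193) = 0.298. This is a difference in means for a continuous outcome and does not translate into power for a time-to-event comparison.

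**Step 3: what a primary MACE analysis would have**

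Inputs from the protocol: 250 per arm, 1:1 allocation, 48 weeks, two-tailed 5% tests by default (Statistical Analysis). Inputs not in the protocol, and therefore assumed: 48-week control risk p (5–20%), hazard ratio HR (0.70–0.90), and all 500 patients followed.

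Formulas (Schoenfeld, 1:1 allocation):

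- Expected events: D = 250 × [p + 1 − (1 − p)^HR]
- m = |ln HR| × √D / 2
- Two-sided power = Φ(m − 1.96) + Φ(−m − 1.96)

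| p | HR | D | m | Two-sided power |
|---|---|---|---|---|
| 5% | 0.90 | 23.8 | 0.257 | 5.8% |
| 10% | 0.85 | 46.4 | 0.554 | 8.6% |
| 10% | 0.70 | 42.8 | 1.166 | 21% |
| 20% | 0.70 | 86.2 | 1.655 | 38% |
| 20% | 0.50 | 76.4 | 3.029 | 86% |

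The last row lies outside the assumed range and shows how strong the effect must be to come near 90%.

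**Step 4: sensitivity**

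- One-sided 5%, the level used for the sample size: 50% power at p = 20% and HR 0.70, and 92% at p = 20% and HR 0.50.
- Only 2 × 193 = 386 patients contributing: two-sided power falls to 31% and 76% for those same two cases.
- Events for 90% two-sided power, 4 × (1.960 + 1.282)² / (ln HR)²: 88 at HR 0.50, 331 at HR 0.70 and 1,592 at HR 0.85. The last exceeds the 500 patients planned.

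**The case against.** The strongest reply is that the intended primary is not really in doubt. LDL-C is called primary in three sections. The overall purpose in the Aims refers to LDL-C. The Abstract's plan to lengthen follow-up if MACE is inconclusive calls MACE the secondary outcome, which a team resting its verdict on MACE would hardly write. The sentence in Statistical Analysis may be a drafting slip. That is a fair reading and it guides the fix. But a slip in the section that prescribes the tests still has to be corrected, and that section supplies no primary LDL-C analysis to fall back on.

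If MACE is secondary, the missing MACE rate and hazard ratio are not a defect in themselves. That stands. They matter only because the analysis section calls MACE primary.

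A reader might go further in three ways that the documents do not support:

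- *A non-significant MACE result is almost certain.* The protocol gives no rate or effect. Even within the assumed range, power reaches 38%, and stronger assumptions raise it well above that.
- *The team intends to claim whichever endpoint succeeds, so the false-positive rate rises to 1 − 0.95² = 9.75%.* No text plans this. The figure also needs independent tests and no effect on either endpoint, while the Discussion expects a considerable fall in LDL-C.
- *The sample size section, too, makes MACE secondary, or the Aims rank MACE above LDL-C.* The former never mentions MACE. The latter lists two questions, neither of which is LDL-C, under a purpose that refers to LDL-C.

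**Conclusion.** The contradiction is real and needs no assumption: Statistical Analysis names time to first MACE as the primary efficacy analysis, against the Abstract and Main Outcome Measures, and against the endpoint used in Sample Size Calculation. The stated 90% power refers to LDL-C change to week 4 and cannot be attached to the MACE comparison.

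The size of the shortfall does rest on assumptions. With 5–20% control risk, hazard ratios of 0.70–0.90 and complete follow-up, two-sided power is about 6–38%. It comes near 90% only for much stronger effects. Low power for MACE is therefore likely but not established by the documents. The text must be corrected before any outcome data are examined.

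**What to change.** Replace the first sentence of Statistical Analysis with wording such as: *The primary efficacy analysis is the between-arm comparison of percentage change in LDL-C from baseline to week 4, the endpoint used for the sample size; the week 12 LDL-C change and time from randomisation to first MACE are secondary.*

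Then:

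- Align the Abstract and Main Outcome Measures with the single time point. If week 12 is to stay primary as those sections now have it, state instead how weeks 4 and 12 are tested jointly.
- State in Sample Size Calculation that the 90% power refers to LDL-C at week 4 only and that the MACE comparison is not powered.
- In Aims of the Study, add the LDL-C question as the primary one, with MACE as secondary. Reordering the two existing questions would not help, since neither concerns LDL-C.

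If the sponsor does intend MACE as primary, rewording is not enough and an event-based sample size is needed.

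The recommended change costs wording only and leaves visits and sample size as they are. The downside is that MACE can no longer be presented as a primary result.

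### Superiority is to be assessed on every efficacy endpoint at an unadjusted p<0.05, with no testing order and no deciding time point for MACE, so the chance of a false finding beyond LDL-C is well above 5%

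*Protocol article*

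**What the plan says.** The Statistical Analysis section sets the scope of testing: "The superiority of evolocumab will be assessed for all efficacy endpoint". The same section fixes one threshold, "statistical significance will be established as" p<0.05, and the default direction, "All statistical tests will be two-tailed unless otherwise indicated". It gives no order of testing and no division of alpha.

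Main Outcome Measures places the endpoints in three named tiers:

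- **Primary:** mean percentage change in LDL-C at weeks 4 and 12.
- **Secondary:** MACE, "assessed at week 12 and week 48 post-treatment". The Abstract agrees: "The secondary outcome is the occurrence of MACE after 12weeks and 1year of treatment". Neither section says which time decides.
- **Also investigated:** the proportions of patients below three LDL-C thresholds; "patients’ quality of life as evaluated with the PROMIS 10 scale at week 12 and week 48 post-treatment"; and percentage change to week 48 in inflammatory markers, an open list that names hsCRP, IL-1β and IL-6.

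The word exploratory is not used for any of these.

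Two other statements bear on the point. The Statistical Analysis section opens by basing the primary efficacy analysis on time to first MACE, whereas the Abstract, Main Outcome Measures and Sample Size Calculation make LDL-C primary. The sample size is set "with a one-sided significance level of 5% (α=0.05), a sample size of 193 patients is required for each treatment arm", whereas the analyses are two-tailed by default.

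**The concern.** The concern rests on what the article states. Read together, the superiority sentence and the common threshold let any efficacy endpoint with a nominal p<0.05 support a superiority statement. The tier names do not say otherwise, because the sentence covers all of them.

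LDL-C is expected to fall considerably (Discussion), and the effect on MACE is the first of the two research questions under Aims of the Study. Whatever the trial adds beyond LDL-C lowering will therefore come from these unprotected tests. MACE is the sharpest case. With two assessment times and no deciding one, a week-12 result below 0.05 could be reported as superiority when week 48 does not support it.

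**Working it through.** **The plan's own figures.** The article gives no family-wise error rate to reproduce. The nearest stated figure, 242 per arm, does reproduce: 193/(1 − 0.20) = 241.25, rounded up to 242, or 484 in total. It does not bear on multiplicity.

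**Inputs from the article.** Each test is at two-sided 0.05 (Statistical Analysis). Leave out the primary LDL-C time points, and leave out the three LDL-C threshold proportions because the drug is expected to move them. Two counts of what remains are reasonable:

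- **Five tests,** limited to scheduled items: MACE at two times, PROMIS 10 at two times, and hsCRP (Table 1).
- **Nine tests:** MACE at two times; both PROMIS 10 scores (physical and mental, named under Baseline Assessments and Laboratory Examinations) at two times, which is four; and hsCRP, IL-1β and IL-6, which is three.

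**Assumption.** The correlation ρ between test statistics is not given. A common ρ of 0, 0.5 and 0.8 is used.

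**Formulas.** Assume no effect on any of the k endpoints.

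- Independent tests, either direction: 1 − 0.95^k.
- Independent tests, favouring evolocumab only: 1 − 0.975^k.
- Common correlation ρ, either direction, with c = 1.96: 1 − ∫ φ(u) [Φ((c − √ρ·u)/√(1−ρ)) − Φ((−c − √ρ·u)/√(1−ρ))]^k du. For results favouring evolocumab only, drop the second Φ term.

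**Results.**

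| Tests | Direction | ρ = 0 | ρ = 0.5 | ρ = 0.8 |
|---|---|---|---|---|
| 5 | either | 1 − 0.95^5 = 0.226 | 0.183 | 0.127 |
| 9 | either | 1 − 0.95^9 = 0.370 | 0.269 | 0.166 |
| 5 | favouring evolocumab | 1 − 0.975^5 = 0.119 | 0.092 | 0.064 |
| 9 | favouring evolocumab | 1 − 0.975^9 = 0.204 | 0.135 | 0.083 |

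The single-test reference is 0.05 in either direction and 0.025 in favour of evolocumab.

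**Sensitivity to the correlation structure.** One common ρ across clinical events, quality of life and inflammation is a strong assumption. Suppose correlation exists only within each of those three groups. The nine-test figure, either direction, is then 0.337 for within-group correlations of 0.5, 0.5 and 0.3 (MACE, PROMIS 10, inflammatory markers), and 0.263 when all three are 0.8. The low end of the table needs high correlation between groups as well.

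**MACE pair alone.** For log-rank tests at two looks on accumulating events, ρ ≈ √(week-12 events / week-48 events). The event split is not given, so it is varied:

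- 25% of events by week 12: ρ = √0.25 = 0.50, error 0.091.
- 50%: ρ = √0.50 = 0.71, error 0.083.
- 75%: ρ = √0.75 = 0.87, error 0.073.

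That is about 1.5 to 1.8 times the nominal 5%.

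**The case against.** The strongest reply is that this is a condensed article. Multiplicity rules for secondary endpoints commonly sit in an SAP, which is not shown, and the superiority sentence may only state the type of comparison, in line with a superiority trial. The first part stands as a limit: a missing adjustment is not itself the finding. But the sentence as published extends superiority to every efficacy endpoint at one threshold. An SAP with a hierarchy would contradict it, so it needs correcting in either case.

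Four stronger readings are tempting, and the documents do not support them.

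- **That there is no hierarchy at all.** Main Outcome Measures names three tiers. What is missing is a testing order or alpha rule attached to them.
- **That the error rate is a fixed figure such as 27%.** That value needs nine tests and a common correlation of 0.5, neither of which the article fixes. It also counts results favouring control; in favour of evolocumab the same case gives 0.135. Nine is a high count: Main Outcome Measures names PROMIS 10 as a scale rather than as two scores, and IL-1β and IL-6 appear in neither Table 1 nor the laboratory list. If efficacy endpoints means only LDL-C and MACE, the inflation beyond LDL-C is the 7–9% of the MACE pair.
- **That MACE is planned to be tested in two competing ways.** The Fisher rule is general to discrete variables, and MACE has its own Kaplan–Meier, hazard ratio and log-rank method.
- **That a week-12-only claim, or a claim from PROMIS 10 or the inflammatory markers, is planned.** None is. The text leaves such claims open.

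**Conclusion.** The point holds in a limited form. The published rule assesses superiority on all efficacy endpoints at an unadjusted 0.05, and the one secondary outcome has two assessment times with neither deciding. If there were no effect beyond LDL-C, at least one nominally significant result would occur with probability of about 13–23% (five scheduled tests) to 17–37% (nine tests). In favour of evolocumab only, the probability is about 6–20% against 2.5% for a single test. The MACE pair alone gives 7–9%.

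Every figure depends on an assumed test count and an assumed correlation (0 to 0.8) or event split (25% to 75% by week 12). The direction does not: under each assumption shown, the error exceeds the nominal level. The primary LDL-C time points and the unlisted biomarkers are outside this point.

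**What to change.** 1. Reconcile the opening sentence of Statistical Analysis, which makes time to first MACE the primary efficacy analysis, with the Abstract, Main Outcome Measures and Sample Size Calculation, where LDL-C is primary. Settle in the same edit whether the primary test is one-sided 5% or two-sided. The sequence below assumes LDL-C stays primary, which is the endpoint the sample size was built on.
2. Replace the superiority sentence with a fixed sequence. Test the primary LDL-C endpoint first. If it is significant, test one key secondary endpoint, time to first MACE through week 48, by log-rank in all randomized patients at two-sided 0.05.
3. State that week-12 MACE, the LDL-C threshold proportions, PROMIS 10 and the inflammatory markers are reported as estimates with 95% CIs and without a superiority claim.

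Other schemes that control the error would also serve; this one is simple and keeps every endpoint in the report. It costs a few sentences and needs no new data or patients. The price is that superiority can no longer be claimed for the endpoints in step 3 from a nominal p<0.05.
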